### Study Design and Setting

The SELECT study is a retrospective cohort study with data from 22 hospitals in the Netherlands, including 4 academic and 18 nonacademic hospitals (Figure 2). Other hospitals may be included as the study progresses and we will use routinely collected electronic data from the participating hospitals. The data sets will contain data on hospitalized patients with COVID-19 from the date the first patient was admitted to the hospital in the Netherlands (March 1, 2020) until data transfer (expected May-December 2023). We will use the heterogeneity in therapeutic regimens in time (ie, first, second, and third epidemiological wave), centers (per protocol high-dose corticosteroids or not), and individual patients in the initial databases to address our aims. In a subpopulation of patients, we will use biobank material collected within the Collaboration on Identification, Understanding and Improved Management of patients with infectious diseases study of the Erasmus MC or collected at the Amsterdam University Medical Center (UMC) within the MERMAIDS-ARI, VIS cohort study or the Amsterdam UMC COVID-19 biobank.

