### Data Collection

In WP1, variation in corticosteroid treatment protocols on the ward between centers is evaluated via questionnaires and extraction of data from the electronic patient record. The focus lies on collecting data from centers that use high-dose corticosteroids on the ward directly after admission and subsequently collecting data from centers with low-dose regimens as a comparison. For the data collection of ICU patients (WP2-3), a collaboration with 2 large COVID-19 study groups is started: the Practice of Ventilation in COVID-19 study (ie, PROVENT-COVID) study and the “Practice of Adjunctive Treatments in Intensive Care Unit Patients with Coronavirus Disease 2019” (PROACT-COVID) study [20,21]. The data of interest will be collected in Castor EDC [22], and it will be imported from each center via a secured data transfer system. Corticosteroid data will be collected on a daily basis including type, dose, and administration route. Regarding biobank WP4, a number of serum biomarker levels were already determined during standard COVID-19 care. In case of missing measurements, the stored samples (Tempus tubes) in the biobank can be used. The BALF was collected during routine COVID-19 care in the Amsterdam University Medical Centers and saved in aliquots at −80 °C for further analysis. SARS-CoV-2 viral load will be measured in BALF by using an in-house reverse transcription polymerase chain reaction. Subsequently, other commercially and generally available biomarkers might be determined in serum and BALF later by using a multiplex assay, such as Luminex. For the whole genome transcriptomes analysis, material was collected and saved in blood RNA Tempus tubes.

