### Statistical Analysis

Data will be analyzed on a convenience sample. No sample size calculations are considered for the study nor will they be provided post hoc [23]. The use of high-dose corticosteroids will be defined as a dichotomous variable (yes or no) in primary analysis and as a continuous variable in secondary analysis.

To study between-center variation in corticosteroid dosing strategy, the proportion of individuals who received high-dose corticosteroids will be compared across hospitals. Determinants of receiving high-dose corticosteroids will be evaluated using a multivariable logistic regression model with study center forced in the model. Whether the effects of significant determinants are different across centers will be tested through a determinant × center interaction term added for each determinant, separately.

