In WP1, WP2, and WP3, several statistical analysis approaches will be considered to determine the association between high-dose corticosteroids and outcome, and statistical analyses will depend on the structure of the available data. A multivariable logistic regression model will be used with high-dose corticosteroids as exposure and survival at day 28 as an outcome. Covariates used for adjustment will include age, gender, BMI, smoking status, prior administration of corticosteroids during admission, comorbidity, sequential organ failure assessment score, oxygen saturation, partial pressure of oxygen in arterial blood–fraction of inspiratory oxygen concentration ratio, C-reactive protein, procalcitonin, ferritin, interleukin 6, D-dimer, lactate dehydrogenase, platelet count, lymphopenia, and level of respiratory support. Covariates can be added or removed based on insights from the data set or from the literature. A model might be constructed in which patients are matched on a propensity score based on their probability to receive high-dose corticosteroid treatment. Propensity scores will be determined using a logistic regression model with high-dose corticosteroids as a dependent variable and determinants of high-dose corticosteroids as independent variables. After matching, survival and mortality at day 28 and other outcome parameters will be compared between matched groups using logistic regression. A Cox proportional hazards model might be performed to determine the effect of high-dose corticosteroids on time to death while taking into account the days of administration using time-dependent covariates. Other approaches involving censoring weights for differential loss to follow-up (eg, marginal structural models) or competing risks (eg, joint models) might be explored.

Furthermore, we will use clinical and biological data to perform latent class analysis to search for subphenotypes, which respond more favorably to corticosteroid treatment. This heterogeneity of treatment effect will be evaluated by including the latent class analysis-derived subphenotype, corticosteroid exposure, and an interaction term of the 2 as c-variate in the above-described survival models. Heterogeneity of treatment effect is considered to be present if the interaction term has a *P* value of <.05.

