## Results

The study was funded in December 2021. As of April 2023, data have been collected for a total of 1500 patients, with data collection anticipated to be completed by December 2023. We expect the first results to be available in early 2024.

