## Discussion

The SELECT study is a retrospective multicenter observational cohort study that aims to determine the most optimal dosing and timing of high-dose corticosteroid therapy in hospitalized patients with COVID-19 and to provide a basis for personalized treatment regimens using biomarkers and whole transcriptome analyses. Increasing insight in the pathophysiological pathways that underlie SARS-CoV-2 infection and the efficacy of high-dose corticosteroid therapy could lead to more precise targeting of high-dose corticosteroid therapy, and as a result, could improve patient outcomes.

The necessity of exploring this matter is underlined by the fact that there is currently no consensus regarding the administration of high-dose corticosteroid therapy in patients with COVID-19.

This study design has several strengths. First, no studies have been performed that evaluate the effect of high-dose corticosteroids throughout the entire clinical course of hospitalized patients with COVID-19. Our study will evaluate the effect of high-dose corticosteroids from hospital admission to the ward or ICU, until hospital discharge. Furthermore, our exploration of biomarker and gene expression profiles for targeted corticosteroid therapy represents a first step toward personalized corticosteroid therapy in COVID-19. By using existing research databases and biobanks, successful data collection is assured, and we will be able to include a large number of patients, which increases the generalizability of the results.

Due to the retrospective study design, some methodological considerations require further discussion. A major issue for any observational study is the fact that treatment modalities are not randomly assigned, but rather likely given based on specific patient characteristics or within-center protocols. This nonrandomized assignment is prone to bias by indication. To correct this bias, our initial analysis step will be the identification of factors that contribute to the allocation of corticosteroid treatment. Subsequently, we will examine several statistical approaches, such as the use of propensity scores at the patient level to minimize treatment indication bias.

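### Centre-by-determinant interaction tests over 22 or more hospitals are mildly anti-conservative and unadjusted, and the propensity score is built from treatment predictors rather than from the listed confounders

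*Protocol article*

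**What the plan says.** The Statistical Analysis section of the protocol article models receipt of high-dose corticosteroids with a "multivariable logistic regression model with study center forced in the model". For the determinants that prove significant, it tests whether their effects differ by hospital through a "determinant × center interaction term added for each determinant, separately". No multiplicity control is stated for these tests, although the same section applies Benjamini-Hochberg to the transcriptome comparisons in WP4b. Whether centre is fixed or random is not stated.

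Study Design and Setting gives "data from 22 hospitals in the Netherlands, including 4 academic and 18 nonacademic hospitals" and adds: "Other hospitals may be included as the study progresses". Results reports that "data have been collected for a total of 1500 patients" as of April 2023, over all work packages. For WP1, Data Collection says: "The focus lies on collecting data from centers that use high-dose corticosteroids on the ward directly after admission". Low-dose centres are then added for comparison.

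The Statistical Analysis section also describes a propensity score that might be used for matching, from a logistic model with "determinants of high-dose corticosteroids as independent variables". The Discussion gives the order of work as the remedy for bias by indication: "our initial analysis step will be the identification of factors that contribute to the allocation of corticosteroid treatment". Propensity methods come after that.

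**The concern.** There are two separate weaknesses.

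**The interaction test.** With 22 hospitals as a categorical factor, one interaction for a one-df determinant estimates 21 extra slopes. A hospital contributes to its own slope only if it has patients both on and off high-dose treatment across the values of the determinant. WP1 seeks hospitals by policy, so some may have few patients on the minority treatment. The chi-squared approximation for the 21-df test then becomes poor and some slopes cannot be estimated. Repeating the test for several determinants without adjustment adds ordinary multiplicity. At stake are false statements that prescribing determinants differ between hospitals, or real differences missed.

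**The propensity score.** A score built from whatever determines treatment favours variables that predict treatment only. These add variance and reduce overlap without removing confounding. It can also leave out variables that relate weakly to treatment but strongly to outcome. If determinants are chosen by significance, low power in this step makes such omissions more likely.

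**Working it through.** The article states no power or error figure for this step and says that no sample size is calculated, so there is nothing to reproduce.

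**Inputs from the article.** 22 hospitals; 1500 patients so far.

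**Assumptions.** Centre is a fixed factor. Centres are of equal size. Half of them have a low and half a high proportion on high dose (the article gives no proportions, so a range is shown). The test is two-sided at 0.05. There is one determinant with log odds ratio 0.5, either binary with 30% prevalence or standard normal.

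**Degrees of freedom.** (22 − 1) × 1 = 21. A determinant with k levels costs 21 × (k − 1), and each added hospital costs more.

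**Information per centre.** 1500 / 22 ≈ 68 patients. The expected minority-treatment count is 68p: 1.4 at 2%, 3.4 at 5%, 6.8 at 10% and 13.6 at 20%. Before allowing for covariates, the chance that a centre has no patient on the minority treatment is (1 − p)^68: 25%, 3%, 0.08% and about 0.

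**Simulation.** 800 data sets per scenario with no true interaction; 400 per scenario with slopes varying between centres (SD 0.5) for power. The Monte Carlo standard error of a rejection rate near 8% is √(0.08 × 0.92 / 800) ≈ 1 percentage point.

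| Use, low/high centres | Binary: false rejection | Binary: power | Binary: slopes not estimable (of 22) | Continuous: false rejection | Continuous: power |
|---|---|---|---|---|---|
| 50/50 | 7.4% | 66% | about 0 | 8.0% | 99.5% |
| 20/80 | 8.1% | 50% | 0.6 | 6.9% | 99% |
| 10/90 | 11.4% | 41% | 3.2 | 8.4% | 91% |
| 5/95 | 10.9% | 27% | 9.4 | 9.1% | 73% |
| 2/98 | 0.1% | 2.5% | 17.4 | 6.0% | 38% |

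All rates but one lie between 6% and about 11%. The exception is a binary determinant at 2/98, where the test almost never rejects. With 136 patients per centre, the non-estimable binary slopes fall to 11.6 at 2/98, 3.2 at 5/95 and 0.6 at 10/90.

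**Several tests.** With k independent tests at true level a, the chance of at least one false interaction is 1 − (1 − a)^k. For an illustrative k = 8:
- at 5%: 1 − 0.95^8 = 34%
- at 6%: 1 − 0.94^8 = 39%
- at 11%: 1 − 0.89^8 = 61%

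Most of this is ordinary multiplicity; the rest is inflation of the single test. Correlated determinants would change these figures.

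**Alternative test.** A separate simulation with no true interaction gave about 6% to 10% for the 21-df test, including at 80/20 and 70/15 use. It gave about 4% to 7% for a one-parameter test of the slope variance.

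**Main effects with centre in the model.** The mean estimate was 0.50 to 0.52 (true 0.50) and interval coverage 94% to 97% throughout. Power for a binary determinant fell from 99% at 50/50 to 94%, 73%, 49% and 22% along the same scenarios.

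**Propensity variables.** This point is textual. The outcome model has a list of 18 adjustment covariates chosen as confounders. The propensity model, described a few lines later, is defined by a different criterion: being a determinant of treatment.

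**The case against.** Several objections limit the point, and they stand.

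- **Fixed centre effects are an assumption.** A model with centre forced in could carry a random effect, and a fuller protocol or analysis plan may settle this. The 21 df depends on it.
- **Near all-or-none use is an assumption.** The article also relies on variation between waves and between individual patients. Policy-based collection is described for WP1 only; WP2 and WP3 draw on two existing ICU study groups. At 20/80 or milder the problem is small.
- **The step is secondary.** The definite outcome analysis adjusts for the listed covariates whatever these tests show, and matching is optional.
- **Significance is not stated as the rule for the propensity score.** It is named only as the filter for which determinants get an interaction test.

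A reader might also infer more than the article supports:

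- *That the interaction results feed the propensity score.* The article sends determinants there, and mentions neither interactions nor centre terms in the score.
- *That the determinant estimates themselves are unstable.* They are not; they lose power only.
- *That all 18 listed covariates will be tested for interaction.* Only significant determinants are.
- *That a random centre intercept would rescue matching.* If centre were put into the score, many treated patients could go unmatched. That loss comes from lack of overlap between centres: in a simulation with 95% against 3% use, 11% of treated patients were matched whether centre entered as dummies, a random intercept or a policy covariate. It is no argument for the random intercept.

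**Conclusion.** The point holds in a limited form. If centre is fixed, the interaction test described is mildly anti-conservative at about 68 patients per centre: roughly 6% to 11% against a nominal 5% over most proportions tried, and not adjusted for the number of determinants tested. For binary determinants where use is about 10/90 or more extreme, it also has low power (41% at 10/90 and 27% at 5/95 for a slope SD of 0.5) and several slopes cannot be estimated.

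These sizes rest on equal centres and on the interim total over all work packages. Smaller work-package samples or unequal centres would be worse, and a larger final sample better.

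The propensity point does not depend on the simulation. Defining the score by determinants of treatment is a weaker criterion than using the confounders the article already names. How much harm follows depends on how determinants are chosen and on whether matching is done. Neither point undermines the main adjusted outcome model, but both are cheap to put right.

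**What to change.** 1. State that centre enters the determinant model as a random intercept.
2. For each significant determinant, replace the centre interaction by a single test of a random-slope variance. State the reference distribution, since the null value lies on the boundary.
3. Apply Benjamini-Hochberg, already used in WP4b, across these tests.
4. Build the propensity score from the confounder list given for the outcome model, not from the determinants found in the first step. The article lets that list be changed in the light of the data, so fix it, or give subject-matter reasons for changes, before outcomes are compared.

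The cost is a few sentences and standard mixed-model software; no new data are needed. The downside is a normality assumption for centre effects, which is hard to check with 22 hospitals and may fit poorly if they fall into two policy groups.

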## Methods

### Definition High-Dose Corticosteroids

High-dose corticosteroids are defined as every treatment with dexamethasone >6 mg daily or an equivalent corticosteroid (Table 1). Regarding prior and continuing use of corticosteroids for other conditions, corticosteroids are considered as part of the COVID-19–related intervention when the high-dose threshold is passed.

**Table 1 table1:** Equivalent corticosteroids and dosages (total daily dosing)^a^.

Drug	Equivalent dose (mg)	Low-dose (mg)	High-dose (mg)
Dexamethasone	0.75	≤6	>6
Cortisone	25	≤200	>200
Hydrocortisone	20	≤160	>160
Prednis(ol)one	5	≤40	>40
Methylprednisolone	4	≤32	>32
Bethamethasone	0.75	≤6	>6

^a^This table shows the equivalent corticosteroids and dosages. The equivalent dose is derived from Farmacotherapeutisch Kompas [18].

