### Patient Selection and Inclusion Criteria

Adult patients (≥18 years) hospitalized with polymerase chain reaction–confirmed COVID-19 or high clinical suspicion of COVID-19 will be included (Figure 3). Pregnant patients and patients receiving corticosteroids for other conditions during or prior to hospital admission are eligible, although a prespecified sensitivity analysis excluding these patients will be performed. Patients who die within 48 hours after admission or patients who object to participate will be excluded from the study. In WP1 and WP4, we will include patients from all SARS-CoV-2 epidemic waves, and in WP2-3, we will include patients from the first and second waves only. Specific inclusion and exclusion criteria for each work package will be applied. In WP1A, patients will be included who are admitted to the ward with a World Health Organization clinical progression scale class of 4-5 [19] (ie, no oxygen or oxygen therapy via a cannula or [non-rebreather] mask). WP1B includes patients who have progressed to the World Health Organization clinical progression scale class of 5-6 (ie, noninvasive oxygen therapy, including conventional oxygen via cannula [non-rebreather] mask, high-flow nasal cannula, noninvasive continuous positive airway pressure, and noninvasive bilevel positive airway pressure) after in-hospital treatment with 10 days of 6 mg per day dexamethasone. The study population for WP2-4 consists of patients admitted to the ICU for a period exceeding 48 hours, who received invasive mechanical ventilation via an endotracheal tube, a tracheostomy, or extracorporeal membrane oxygenation during their ICU stay.

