### Interventions

Patients were administered with >6 mg dexamethasone or an equivalent corticosteroid for a minimum of 3 consecutive days (Table 1). Our study permits the use of other general concurrent interventions, such as venous thromboembolism prophylaxis, fever and glucose control, fluid management, antibiotics, and antiviral drugs. The use of other immunomodulatory agents such as baricitinib, JAK inhibitors, and interleukin 6 pathway inhibitors, as well as antiviral drugs such as remdesivir, is allowed as part of a clinical trial or hospital policy. However, a sensitivity analysis will be performed excluding these patients.

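### WP1–WP3 commit only to a day-28 logistic model on a fixed yes/no high-dose exposure, which builds in immortal-time bias if early deaths count as unexposed; the time-dependent analysis is optional

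*Protocol article*

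**What the plan says.** All references are to the Methods of the protocol article.

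- **Model.** Statistical Analysis states, for WP1–WP3: "A multivariable logistic regression model will be used with high-dose corticosteroids as exposure and survival at day 28 as an outcome". This is the only effect model for those work packages stated without a conditional.
- **Exposure coding.** The same section says: "The use of high-dose corticosteroids will be defined as a dichotomous variable (yes or no) in primary analysis".
- **What counts as high dose.** Interventions: "Patients were administered with >6 mg dexamethasone or an equivalent corticosteroid for a minimum of 3 consecutive days". Definition High-Dose Corticosteroids: "High-dose corticosteroids are defined as every treatment with dexamethasone >6 mg daily or an equivalent corticosteroid", with no minimum duration.
- **Alternatives.** Propensity matching is optional, and the matched groups would again be compared by logistic regression. For timing: "A Cox proportional hazards model might be performed to determine the effect of high-dose corticosteroids on time to death". Beyond that: "Other approaches involving censoring weights for differential loss to follow-up (eg, marginal structural models) or competing risks (eg, joint models) might be explored". The censoring weights there are offered for loss to follow-up, not for when treatment began.
- **Early deaths.** Patient Selection and Inclusion Criteria: "Patients who die within 48 hours after admission or patients who object to participate will be excluded from the study". WP2–WP4 also require more than 48 hours in the ICU.
- **Data.** Data Collection says that corticosteroid type, dose and route are recorded daily.

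**The concern.** A patient can be coded as exposed only after living long enough to start high-dose treatment and, under the Interventions wording, to complete 3 days of it. If those who die sooner fall into the comparison group, the exposed group carries survival time that was guaranteed by its definition, and the comparison group collects the early deaths. Baseline covariates and a propensity score do not repair this, because the fault lies in how exposure is classified and not in who is likely to be treated. The 48-hour exclusion is shorter than 3 days and does nothing for later starts.

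Later starts are to be expected. The Introduction says that high-dose treatment is given mainly late in the course. Timing is one of the two headline aims, and the Discussion hopes the results could inform guidelines and hospital protocols.

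**Working it through.** The article gives no sample size, event rate or expected effect, so there is no figure of its own to reproduce. The check asks what the stated analysis returns when treatment has no effect.

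**Assumptions (not in the documents).** 28-day mortality *m* = 15–40%; constant hazard; share intended for high dose *p* = 30–50%; start times as listed below; patients who die before qualifying as exposed counted as unexposed.

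**From the article.** Minimum treatment *d* = 3 days (Interventions) or 0 (definition section); deaths before *x* = 2 days excluded. For WP1B/WP3, time zero is set at the end of the 10-day course, with *x* = 0 and 28 days counted from there.

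**Formulas.**
- *h* = −ln(1 − *m*)/28
- *s* = 1 − *m* (alive at day 28)
- *g* = exp(−*xh*) (alive at the end of the exclusion window)
- *q* = mean over start times *S* of exp(−*h*·max(*S* + *d*, *x*)) (alive when exposure is established)
- Deaths per survivor: exposed (*q* − *s*)/*s*; unexposed [(1 − *p*)(*g* − *s*) + *p*(*g* − *q*)]/[(1 − *p*)*s*]
- OR = (1 − *p*)(*q* − *s*)/[*g* − (1 − *p*)*s* − *pq*]

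**Worked values, *m* = 30%, *p* = 50%.** *h* = 0.012738, *s* = 0.7, exp(−2*h*) = 0.97485, exp(−3*h*) = 0.96251.
- From admission, 3-day rule: *q* = 0.96251; OR = 0.13125/0.14359 = 0.91.
- Starts uniform over days 0–7, 3-day rule: *q* = 0.96251 × (1 − e^(−7*h*))/(7*h*) = 0.92084; OR = 0.11042/0.16443 = 0.67.
- Same starts, no minimum: *q* = [2e^(−2*h*) + (e^(−2*h*) − e^(−7*h*))/*h*]/7 = 0.95313; OR = 0.12657/0.14828 = 0.85.
- WP1B/WP3, immediate start, 3-day rule: *g* = 1, *q* = 0.96251; OR = 0.13125/0.16875 = 0.78.
- WP1B/WP3, starts over 4 days, 3-day rule: *q* = 0.93840; OR = 0.11920/0.18080 = 0.66.

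**Ranges over *m* = 15–40% and *p* = 30–50%.**

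| Setting | 3-day rule | No minimum |
|---|---|---|
| Treatment from admission | 0.91–0.94 | 1.00 |
| Starts over days 0–7 | 0.66–0.76 | 0.85–0.90 |
| WP1B/WP3, immediate start | 0.76–0.84 | 1.00 |
| WP1B/WP3, starts over 4 days | 0.64–0.75 | 0.84–0.89 |

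A simulation of 2,000,000 patients per scenario (*p* = 50%) agrees to within 0.01. With a declining hazard (Weibull shape 0.7, *m* = 30%, *p* = 50%) the bias grows: 0.86 from admission and 0.58 for days 0–7, both with the 3-day rule.

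**Does the remedy work?** On null data with *m* = 30% and starts over days 0–7, the fixed yes/no analysis gives an OR of 0.67. Time-updated exposure gives a rate ratio of 1.00, a day-10 landmark gives an OR of 0.99, and grouping by intended treatment gives 0.99.

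**The case against.** The strongest reply is that the article does not fix as much as this suggests. Each part of it has some force.

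- **No model is labelled main.** Statistical Analysis says that several approaches will be considered, depending on the data, and the abstract promises longitudinal modelling. A yes/no exposure can also be time-updated. A reader might infer that the ever/never logistic model is the declared main analysis; the text does not say so. What stands is that the model without timing is the firm one, while for the other "A Cox proportional hazards model might be performed" is all that is said.
- **The 3-day rule is not settled.** The definition section has no minimum. Without it the bias vanishes for treatment from admission, but remains for later starts.
- **The handling of early deaths is not stated.** Patients who die before completing 3 days might be excluded rather than counted as unexposed. For treatment from admission the OR is then (*q* − *s*)/(*g* − *s*) = 0.26251/0.27485 = 0.96 at *m* = 30%: smaller, but not gone.
- **WP1A and WP2 concern initial treatment**, and WP1 data collection focuses on centres that treat directly after admission. For strictly initial treatment the bias is small. The days 0–7 figures apply only if later starters are counted as exposed.
- **Direction.** A reader might infer that an ineffective treatment would necessarily look beneficial. The documents do not support that as a net result. The Introduction says that high dose goes mainly to the most severely ill, and the Discussion acknowledges bias by indication, which may push the other way. If comparators had to complete 10 days and exposed patients only 3, the null OR would be (e^(25*h*) − 1)/(e^(18*h*) − 1) = 1.42–1.49 for *m* = 15–40%.
- **Analysis-plan detail.** Grace periods and weights can properly wait for the statistical analysis plan. The model and exposure coding criticised here are stated in the article.

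**Conclusion.** The concern holds in a limited form. In WP1–WP3 the only firm effect model uses a fixed exposure that may depend on survival after follow-up begins, and the analysis that would respect timing is optional. If early deaths are counted as unexposed, the distortion favours high dose. It is slight for treatment from admission (null OR 0.91–0.94 with the 3-day rule, 1.00 without) and material for later starts and for WP1B/WP3 (0.64–0.84 with the rule, 0.84–1.00 without). These sizes rest on the assumed mortality, share treated and start times; the direction of this one bias does not, given that classification. The net direction of the final estimate is unknown.

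Two further readings should be resisted. Starts spread over days 0–14 from admission give null ORs near 0.5, but they do not describe WP1B or WP3, where both groups have already completed the 10-day course. Nor does the point extend to WP4a, which commits to a marginal structural model. The calculation covers death by day 28. WP1A has other primary outcomes (high-flow or invasive ventilation, or hospital mortality under care restrictions); the same classification problem arises there, but its size was not computed.

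**What to change.** 1. Reconcile the Definition High-Dose Corticosteroids and Interventions sections on what counts as exposed, and state how patients who die before meeting the criterion are classified.
2. State time zero separately for WP1A, WP1B, WP2 and WP3, and count follow-up from it.
3. Make a time-aligned analysis primary in WP1–WP3. Either classify patients by the regimen started at time zero, or use the daily dosing data for time-updated exposure, a landmark analysis, or cloning with censoring and weighting.
4. In WP1A, apply the same alignment to its own primary outcomes.
5. Keep the ever/never logistic model as a sensitivity analysis only.

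The cost is more programming and somewhat wider intervals. No new exposure data are needed.
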